## Groups:

The eligible patients will be enrolled in this double blinded study and randomly allocated into one of two parallel equal groups (15 patients in each group) according to sample size by computer generated random number lists. The allocation will be concealed using closed opaque envelopes. Both the patient and the investigator who collected the data after the block will be blind to the study group.

- Multifidus plane block (MPB) group(n=15): Participants will receive injection volume of 1 ml.kg of 0.25% bupivacaine at the fascial plane between the multifidus muscle and the median sacral crests of S2 and S3. (**Suresh *et al.*, 2018; Mahajan *et al.*, 2021**)
- Caudal block (CB) group (n=15): Participants will receive 1 ml.kg of 0.25% bupivacaine, between the two sacral cornua. (**Campbell, 1933; Suresh *et al.*, 2018**)

## Block Technique:

### - MPB group;

The child will be turned prone and the sacral area will be prepared and sterilized. A linear ultrasound probe (2.5-7.5MHZ) of ultrasound machine (Sonosite turbo M, Bothell, Washington, USA) will be used. Targeting the fascial plane between the multifidus muscle and the median sacral crests of S2 and S3. The block needle is inserted using the “in-plane” technique.

### -CB group

- In the left lateral position, CB will be done.

- The ultrasound transducer was first placed transversely at the midline to obtain the transverse view of sacral hiatus. At this level, the ultrasound transducer is rotated 90 degrees to obtain the longitudinal view of sacral hiatus. The block needle is inserted using the “in-plane” technique.
- After completing the block injection, the patient will be immediately placed in the supine position, IV Ringer’s solution 10 ml/kg/hour will be administered throughout the surgery.

Potential complications of the blocks:

- 1- Haemodynamic/systemic or local adverse events. Examples include arrhythmia, hypotension when combined with general anaesthesia.
- 2- Systemic toxic events from local anaesthetics may involve cardio- or neurotoxicity. Current guidelines recommend that any haemodynamic deterioration should be treated by Intralipid 20% as first-line therapy
- 3- Toxicity-related seizures that need to be treated with propofol, benzodiazepines, or barbiturates.
- 4- Infection/inflammation of the puncture site, sacral osteomyelitis, or local nerve injury which can be avoided by good sterilization before the block.
- 5- Inability to place the block and block failure, so children are generally sedated to ensure immobility during the puncture.
- 6- Local nerve injury, During MPB care must be taken not to inject directly into the posterior sacral foraminal, which lie lateral to the intermediate sacral crests.

Measurements:

The primary outcome of the study is to use the first time to rescue analgesia postoperative analgesic after two different block techniques to compare the analgesic effect.

The secondary outcome is to compare the two methods for;

- Hemodynamic parameters.
- The total intraoperative IV fentanyl requirements in µg.
- postoperative FLACC pain score and complications.

-Intraoperative:

- Hemodynamic parameters (heart rate and mean arterial pressure) and SpO2 will be measured and recorded just after performing the block and at 15 min interval till the end of the surgery.
- The total intraoperative IV fentanyl requirements in µg, anesthesia time in minutes (from induction of anesthesia till awake extubation), and surgical time in minutes (from skin incision until skin closure) will be recorded.

After the end of surgery, reversal of the atracurium will be done by giving neostigmine in a dose of 0.04 mg/kg and atropine in a dose of 0.02 mg/kg then awake extubation of the patients was done.

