**1-Pre-operative settings:**

Detailed preoperative history will be taken from the parents of the child for any medical disorder, physical examination and preoperative investigations (complete blood picture, Bleeding Time, prothrombin time and partial

thromboplastin time) will be performed. Age and weight will be recorded. The patient will be fasting according to guidelines preoperatively.

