## 2-Intra-operative Settings

Inside the operating room, mean arterial blood pressure (MAP), heart rate (HR), electrocardiography (ECG) and peripheral oxygen saturation (SpO2) will be obtained using standard non-invasive monitors and base line values will be recorded.

General anesthesia will be induced using face mask with sevoflurane (4-8%) in 80% oxygen, then an intravenous (IV) cannula will be secured. Patients aged (1-4) years an One µg/kg fentanyl will be given and intubation will be facilitated by 0.5 mg/kg atracurium, While Patients aged 4-6 years will receive fentanyl 1 µg/kg, propofol 1-2 mg/kg and intubation will be facilitated by 0.5 mg/kg atracurium. Isoflurane 1%-2% with oxygen was used for anaesthetic maintenance. After stabilizing the patient's hemodynamics and before skin incision, the blocks will be done. (Ozen and Yigit, 2020)

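### Intraoperative fentanyl is compared as an unscaled µg total in children aged 1–7, apparently counting a pre-block per-kg dose, which costs power on this secondary outcome

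*Protocol*

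**What the plan says.** Under Measurements (within the section headed -CB group), the Protocol lists this secondary outcome as "The total intraoperative IV fentanyl requirements in µg" and repeats it in the intraoperative recording list: "The total intraoperative IV fentanyl requirements in µg, anesthesia time in minutes". The unit is given both times and neither entry divides by weight. The start of the counting period is not stated, although the same list defines start and end points for anesthesia time and surgical time.

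The section on intra-operative settings describes induction. In the younger band "One µg/kg fentanyl will be given and intubation will be facilitated by 0.5 mg/kg atracurium"; the older band "will receive fentanyl 1 µg/kg, propofol 1-2 mg/kg". The block comes later: "After stabilizing the patient's hemodynamics and before skin incision, the blocks will be done". No further fentanyl dose, trigger or expected amount is given.

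Inclusion Criteria set the age range at 1 to 7 years. Under the pre-operative settings, "Age and weight will be recorded", but weight is not linked to this outcome. The section on analytical statistics names the t-test and the Mann-Whitney U test, both unadjusted. Allocation is by computer-generated random lists, 15 per group, with no mention of stratifying by age or weight.

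**The concern.** Fentanyl is given by weight and the children's weights will vary widely, so a µg total mixes how much each child needed with how heavy the child is. If the induction dose is counted, every child's total also contains 1 µg for each kg of body weight, given before any block was placed. A child who needs nothing further would then score a number of µg equal to body weight in kg.

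This is the only dose-based measure of intraoperative analgesia in the trial; the other intraoperative outcome, hemodynamics, is indirect. With 15 children per arm there is little power to spare, and a real difference between blocks could be missed because of weight-related noise that the investigators can remove with data they already collect.

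**Working it through.** The protocol states no figure for this outcome, so there is none to reproduce. The check asks how much precision depends on the unit and on whether the induction dose is counted.

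**Inputs from the Protocol.** 15 per arm; induction fentanyl 1 µg/kg before the block; ages 1–7. The induction bands as written reach age 6 while eligibility reaches 7. Those passages need to be reconciled, but I take 1 µg/kg for all children here.

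**Assumptions (not in the Protocol).** Age uniform on 1–7 and weight about 2 × (age + 4) kg with 10% scatter, which gives mean 16 kg and SD about 3.8 kg. Supplementary fentanyl S after the block averages 0.5 versus 1.0 µg/kg, SD 0.5 or 0.4, independent of weight W. Two-sided 5% t-test.

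**Formulas.** The raw total is T = W(1 + S), the raw post-block amount is WS, and the scaled outcome is S. With a = 1 + mean(S) for T, or a = mean(S) for WS:

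Variance = a² × 3.8² + 16² × SD² + 3.8² × SD²

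The share explained by weight is the first term divided by the whole. In both raw versions the difference in means is 16 × 0.5 = 8 µg.

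**Numbers at SD 0.5.**
- Raw total: variances 32.5 + 64 + 3.6 = 100.1 and 57.8 + 64 + 3.6 = 125.4. Average SD 10.62, standardised effect 8/10.62 = 0.75. Weight share 32% and 46% in the two arms.
- Raw post-block: variances 3.6 + 64 + 3.6 = 71.2 and 14.4 + 64 + 3.6 = 82.0. Average SD 8.75, effect 8/8.75 = 0.91. Weight share 5% and 18%.
- Post-block µg/kg: effect 0.5/0.5 = 1.00.

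At SD 0.4 the corresponding effects are 8/9.40 = 0.85, 8/7.23 = 1.11 and 0.5/0.4 = 1.25.

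**Power, 15 per arm.**

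| Outcome | SD 0.5, formula | SD 0.5, simulation | SD 0.4, formula | SD 0.4, simulation |
|---|---|---|---|---|
| Raw total with induction | 0.51 | 0.49 | 0.61 | 0.60 |
| Raw post-block µg | 0.68 | 0.67 | 0.83 | 0.83 |
| Post-block µg/kg | 0.75 | 0.75 | 0.91 | 0.90 |

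The small differences arise because the simulation floors supplements at zero. In it, weight explains about 40–45% of the variance of the raw total and about 13–16% once induction is excluded (11–13% if the two arms are pooled).

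**Wider range.** Weights were drawn uniformly on 10–20 or 9–25 kg, with skewed supplements averaging 0.25–2.0 µg/kg (SD 0.25–1.0) and the Mann-Whitney test, in 16 scenarios.
- Where the arms truly differ, power is 0.31–0.86 for the raw total and 0.51–0.98 for µg/kg, and µg/kg is higher every time.
- Weight explains 13–63% of the variance of the raw total, and 1–22% without induction.
- Where the arms do not differ, the false-positive rate is about 0.04–0.05 on either scale.

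**Chance imbalance.** The standard error of the difference in mean weight is 3.8 × √(2/15) = 1.39 kg, so a gap above 2 kg arises in about 15% of randomisations.

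**The case against.** The strongest objection is that the Protocol never says the induction dose counts. It speaks of requirements, and a fixed dose given to every child is arguably not one. Most of the loss depends on this point. Without the induction dose, the unit alone costs about 7–8 points of power (0.67 versus 0.75; 0.83 versus 0.90), not 26–30 (0.49 versus 0.75; 0.60 versus 0.90). That stands, and inclusion must be presented as an inference. The inference is still the more natural one: the word total is unqualified, and induction sits under the heading "2-Intra-operative Settings". If the other reading was intended, the window still needs stating, because two data collectors could record different totals.

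A reader might infer that the outcome largely measures body weight. That is not supported in general. Weight explains about 40–45% of the variance in the main illustration and more than half in only 3 of the 16 wider scenarios. The case where µg equals kg applies only to children given no supplement, and the Protocol does not say how many that would be. The induction dose may well be most of the amount given (53–85% under the wider assumptions), but a share of the dose is not a share of the variance.

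A reader might also infer that the comparison is biased. It is not: allocation is random and concealed, and chance weight imbalance is part of the sampling error that the test already allows for.

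Finally, the outcome is secondary and does not bear on the sample size, and recorded weight leaves a per-kg analysis possible later. This limits the severity but does not remove the point, since the unit is fixed in the text.

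**Conclusion.** The point holds as a loss of precision in one secondary outcome. Two things are certain from the text: the unit is raw µg with no weight scaling, and the start of the counting window is not stated. That the pre-block induction dose is counted is a strong inference. Under the main assumptions, moving from the raw total with induction to post-block µg/kg raises power from about 0.49–0.60 to 0.75–0.90. Roughly two thirds or more of that gain comes from dropping the induction dose (0.18 of 0.26 at SD 0.5; 0.23 of 0.30 at SD 0.4), and the rest from scaling. The direction holds across all the assumptions tried. The size does not come from the Protocol and should be read as an illustration. The primary outcome is unaffected. The change should be made, but the trial does not depend on it.

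**What to change.** Under Measurements, define the outcome as IV fentanyl given from completion of the block until the end of surgery, in µg per kg of the weight recorded before surgery, excluding the induction dose. State this definition in both places where the outcome appears. Log the induction dose separately from later doses. The raw µg total may still be reported descriptively.

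The cost is one additional field on the record form. Weight is already collected, and no dose, trigger or other clinical rule changes.

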### 3- Post-operative settings:

- FLACC pain score

FLACC is a behavioural pain assessment scale used for nonverbal or preverbal patients who are unable to self-report their level of pain. Pain is assessed through observation of 5 categories including face, legs, activity, cry, and consolability.

- The obtained score will be recorded by a blinded investigator immediately after recovery, then at 2-4-6-12-18 and 24 hours postoperatively.
  - Time to first analgesic rescue will be calculated in hours from the recovery of the patient till the first analgesic request (FLACC score  $\geq 3$ ).
  - Duration of analgesia in hours after awake extubation until the first analgesic request; including diclofenac sodium suppository in a dose of 0.5 mg/kg and the incidence of any side effects such as respiratory depression, urine retention, hematoma, nausea, vomiting, nerve injury, or infection will be recorded. (Joseph et al., 2011)
- Statistical Methods: The collected data will be revised, coded, tabulated, and introduced to a PC using SPSS software version 22. Data will be presented, and suitable analysis will be done according to the type of data obtained for each parameter. Data will be tested first for normality.

#### 1-Descriptive statistics:

- Mean, standard deviation (SD) and range for parametric numerical (quantitative) data.
- Median and inter-quartile range (IQR) for non-parametric data.
- Frequency and percentage of categorical (qualitative) data

#### 2-Analytical statistics:

- Independent-samples t-test of significance was used when comparing between two means.
- Chi-square (X) test of significance was used in order to compare proportions between two qualitative parameters.
- Mann Whitney U test: for two-group comparisons in non-parametric data.
- The confidence interval was set to 95% and the margin of error accepted was set to 5%. So, the p-value was considered significant as the followings:

- Probability (P-value):

P-value  $<0.05$  was considered significant.

P-value  $<0.001$  was considered as highly significant.

P-value  $>0.05$  was considered non\_significant.

